## Abstract

**Background:**

Collaborative Assessment and Management of Suicidality (CAMS) is a therapeutic framework that appears promising to reduce suicidal ideation and suicidal cognition. CAMS has not previously been evaluated in a standard specialized mental health care setting for patients with suicidal problems in general. In this pragmatic randomized controlled trial (RCT) we will investigate if CAMS is more effective than treatment as usual (TAU) in reducing suicidal thoughts and behaviors. Effects will also be investigated on mental health and symptom relief in general and upon readmissions to inpatient units.

**Methods/design:**

The study is a multicenter, observer-blinded, superiority, two-armed RCT which will include patients from four clinical departments at Vestre Viken Hospital Trust, Norway. We aim to include 100 patients with moderate to strong suicidal problems, as defined by a score of 13 or more on Beck’s Scale for Suicide Ideation - Current. Patients are included regardless of diagnosis. Randomization will be performed using a stratified four-block procedure with treatment unit as the stratification variable. The duration of treatment will vary depending on patients’ needs and clinical assessments. Patients are interviewed by research staff at four checkpoints: baseline, 2 weeks, 6 months, and 12 months. Central outcome measures are the Beck Scale for Suicide Ideation - Current, Outcome Questionnaire – 45, and Suicide Attempt Self-Injury Count.

**Discussion:**

This pragmatic trial is effectuated within the Public Health Care System in Norway, where patients have multiple problems and diagnoses and therapists have a high work load. Results from this trial are highly generalizable to a typical everyday clinical setting, and one should expect similar results if CAMS is implemented in the future as a standard component in specialized mental health care systems.

**Trial registration:**

Open Science Framework: DOI 10.17605/OSF.IO/JHRM2. Registered 5 July 2015. ClinicalTrials.gov: NCT02685943. Registered on 8 February 2016.

## Background

By publishing its first World Suicide Report “Preventing suicide: a global imperative,” the World Health Organization (WHO) put suicide on the agenda worldwide [1]. The WHO’s goal is a 10 % reduction in the occurrence of suicide by 2020 through raising awareness, systematically mapping occurrences, and developing nationally tailored suicide prevention strategies within the general population and health services in particular. At a global level, approximately 800,000 people die by suicide each year, making suicide one of the leading causes of death worldwide. Suicide deaths, along with suicidal ideation and attempts, have a profound impact on society in the form of bereavement as well as on various public health issues and related economic factors.

In Norway, the suicide rate is 11.2/100,000; 500–600 lives are lost to suicide annually. In addition, attempted suicides are believed to be as many as 10 times higher or more than rates of completions. A national guideline for preventing suicide within specialized mental health services was published and gradually implemented since 2008 [2]. Despite the growing awareness both within public health and specialized fields such as mental health facilities, the rates of suicide remain relatively stable dating back to 1996 [3].

Mental illness is a known risk factor for suicide; affective disorders, psychosis, substance abuse, and personality disorders are commonplace among suicide completers. It is estimated that as many as 45–90 % of those who die by suicide suffer from mental illness [4, 5]. Suicide-related presenting problems are involved in 50–70 % of all admissions to specialized mental health care services in Norway [6, 7]. Concomitantly, people who have received inpatient treatment in the mental health care services are especially vulnerable. The first weeks following discharge are notably associated with increased suicidal risk [8]. Accurate risk assessment and effective treatments for at-risk patients are imperative.

As people suffering from mental illnesses seem to be disproportionally overrepresented in the suicidal fatality statistics, it is essential to develop effective treatment models. However, remarkably little research exists on which treatments are the most effective, and evidence-based treatment models for suicidal patients are rarely disseminated in clinical practice [9]. Most suicidal patients within mental health care are treated with therapies that are not yet empirically validated for effectively treating suicidal risk [10]. There are a few exceptions, however. For example, dialectical behavior therapy (DBT) has been effective for suicidal patients with emotionally unstable (borderline) personality disorder [11]. Likewise, cognitive therapy for suicide prevention (CT-SP) has received support as an effective treatment in preventing suicide attempts for adults who recently attempted suicide [12, 13]. For more information, see a recent review on effective psychological treatments for suicidal risk by Jobes and colleagues [14].

For suicide-related problems, a small set of novel approaches have been developed. Among these promising approaches is the “Collaborative Assessment and Management of Suicidality” (CAMS) for assessing and treating suicidal patients using a problem-focused suicide-specific approach [15]. CAMS is a therapeutic framework that emphasizes collaborative assessments of a patient’s suicidal state and a problem-focused treatment that centers on patient-defined suicidal “drivers” (those problems that make suicide compelling to the patient). To date, CAMS is supported by a range of clinical treatment studies including seven correlational trials and two randomized controlled trials (see Andreasson et al. [16]; Jobes [17]; Comtois et al. [18]). As such, CAMS may have the potential to address a common critique raised against clinical suicide prevention efforts both in Norway and internationally: there has been a disproportionate focus on mechanical risk assessments at the expense of developing and conducting effective suicide-specific treatments [19, 20]. The current trial is one initiative that may contribute to the further development within the field of clinical suicidal prevention by comparing CAMS to “treatment as sual” (TAU) within a randomized controlled trial for suicidal patients in Vestre Viken Hospital Trust.

### The CAMS approach

CAMS is a psychotherapeutic framework developed by David Jobes [15]. As a semi-structured therapeutic framework, CAMS is guided by both a philosophy and specific therapeutic strategies that amplify active collaboration between the patient and the therapist, while assessing and treating the subjective underlying factors or drivers of suicidality [21]. Moreover, CAMS is designed to create a strong clinical alliance increasing the patient’s motivation to want to live.

Within the CAMS approach to suicidal risk, there is the central use of a multipurpose assessment, treatment planning, tracking, and outcome tool called the Suicide Status Form (SSF). In brief terms, the SSF uses both quantitative and qualitative assessment ratings of five central suicide markers previously described by Shneidman, Beck, and Baumeister: psychological pain, stress, agitation, hopelessness, and self-hate. In addition to rating these constructions on a 1–5 rating scale, the patient is encouraged to describe the qualitative aspects of each entity in such a way that the problem areas that contribute to suicidality are clarified. Further on in the initial CAMS assessment, the patient identifies reasons for living and reasons for dying, as well as his/her wishes to live and wishes to die. The SSF has various formats: for the first session, all interim sessions, and the outcome/disposition session. In every CAMS session, however, the dyad begins with assessment of the key markers and ends with a side-by-side seating to review and update both the stabilization plan and the driver-oriented treatment plan. As a part of the CAMS approach and structure, the patient and therapist collaboratively develop a suicide-specific treatment plan that continues to identify, target, and treat the drivers of the patient’s suicidality. CAMS is described as “non-denominational,” which means the framework can be used across disciplines and can be effectively used transtheoretically as long as the provider follows the philosophy and clinical structure indicated by the SSF format. CAMS clinicians are empathetic of suicidal states and pursue suicide-specific treatment in a supportive, collaborative problem-solving, non-judgmental manner.

There is fairly robust and replicated evidence that CAMS is superior to other approaches for suicidal ideation and suicidal cognition [17, 22]. The overall CAMS approach has received preliminary support in seven non-randomized outcome studies. These include various correlational studies that support the usefulness of the approach in both outpatient and inpatient settings [23–25]. To date, well-powered randomized controlled trials are limited, but one small RCT conducted by Comtois and colleagues showed CAMS to be superior to TAU in terms of reduced suicidal ideation and symptom severity and increased hope, retention, and superior patient satisfaction [18]. A new Danish superiority RCT compared treatment conditions for borderline personality disorder with self-harm and suicidal behavior [26]. In this somewhat underpowered RCT, the investigators found no significant difference between DBT and CAMS for self-harm and suicide attempts at 28 weeks following treatment, which was surprising, given the robust evidence of the effectiveness of DBT for self-harm and suicide attempt behaviors [16].

#### Aims and research questions

Our aim is to investigate whether CAMS represents improved services to patients with suicidal ideation and elevated suicidal risk in comparison to existing practices. The primary objective is to investigate whether treatment for suicidal patients by using CAMS results in a clinically and statistically significant reduction in suicidal thoughts and behaviors as compared to treatment as usual (TAU). Secondary aims are to investigate effects of CAMS and TAU upon mental health in general, symptom relief, and readmissions. Furthermore, we will test the influence of various moderating variables upon outcome, including qualities of the working alliance, the patients’ initial level of self-efficacy, and substance and alcohol abuse.

## Methods/design

In a pragmatic RCT, CAMS will be compared with TAU in the department of mental health and addiction, Vestre Viken Hospital Trust, Norway. Vestre Viken Hospital Trust consists of several formerly independent hospitals and institutions, covering 26 municipalities with a population base of 470,000 people. The trial will be conducted at four different outpatient and inpatient treatment units situated in four different geographical areas. At Baerum District Psychiatric Center one general inpatient facility and one acute inpatient facility participate in the trial. One acute in-ward facility at a psychiatric hospital in Asker (Blakstad Hospital) also attends the trial. Furthermore, in Drammen District Psychiatric Center one acute ambulatory outpatient unit and one team within the general outpatient clinic participate. Lastly, at Kongsberg District Psychiatric Center two units are involved: one acute inpatient ambulatory team and one team from the general outpatient clinic. Together, the participating inpatient units admitted approximately 850 patients for hospitalization in 2015. The outpatient clinics saw approximately 2000 patients for treatment. Information is not available regarding the proportion of those treatment courses that were associated with suicidality. However, as reported by Ruud in a representative study, up to 70 % of those seeking acute psychiatric health care in Norway suffer from some degree of suicidal-related problems (thoughts, plans, actions) [7]. Similar figures were reported by Mellesdal and colleagues [6].

### Eligibility criteria

Suicidality can be viewed as a transdiagnostic issue that often increases with symptom severity. Hence, broad inclusion criteria are meaningful in our clinical setting.

#### Inclusion criteria

The inclusion criteria are as follows:Newly referred adults above 18 years of ageSymptom severity and complexity that require health care and treatment within specialized care in NorwayOngoing moderate to severe suicidal thoughts, plans, or actions within the past 2 weeks, qualifying to a score of 13 or more on the Beck Scale for Suicide Ideation - Current (BSSI-C)Ability to provide informed consent

#### Exclusion criteria

The exclusion criteria are as follows:Age less than 18 yearsSymptom severity and complexity beneath the threshold that elicits rights to necessary health care within specialized care in NorwayKnown or previously diagnosed intellectual disability or dementiaKnown or previously diagnosed developmental disorder such as autism or Asperger’s syndromeOngoing psychosis in terms of active hallucinations and delusions which hamper the ability to provide informed consentPoor Norwegian acquisition which requires a professional translator during the research interviews or the therapeutic processPrevious exposure to CAMS treatment components

The main principle that we follow is that project participants may be included if the symptoms are above threshold as measured by the BSSI-C. The role of informed consent for participation is detailed in the section “Ethics approval and consent to participate.”

The electronic patient journal contains information regarding previous diagnosis and is accessible to the research team and aids the inclusion/exclusion process. If research assistants or clinicians in companionship suspect that an eligible participant has a developmental disorder or intellectual disability, the participant is not recruited into the project for further screening but follows usual treatment procedures in the clinic. If such information or diagnosis is made post hoc after inclusion, the participant will be excluded from further participation. Whether Norwegian language acquisition level is sufficient for inclusion was pragmatically decided to be a clinical judgment, whereby participants with need of a translator during assessment or therapy were excluded. If a patient presents with active psychotic symptoms in terms of hallucinations or delusions, she/he is not invited to participate. If such functioning is identified during the screening process (e.g., by MINI), the patient will be excluded from the trial and will continue with ordinary treatment in the clinic.

Finally, we exclude patients with previous exposure to CAMS treatment components, most notably patients who previously have been administered the SSF. As the entire hospital shares the same electronic patient journal system, we are able to check this before recruiting patients. Use of antidepressants or other kinds of medications is permitted; however, we will register and map their occurrence.

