Interested patients will meet a project assistant who provides thorough and written information about the aim of the study, the study design, and procedures. Ethics, data collection and storage of information, confidentiality, and the possibility to withdraw from the project at any time are also covered in these meetings. All screening interviews with research assistants will be conducted at the clinical unit already familiar to the patient. If an informed consent is offered by the patient, the research assistant follows up with the inclusion screening interview BSSI-C. Eligible participants who are actively suicidal as indicated by a positive score on item SS104 or SS105 and who score 13 or more are accepted for inclusion. At this point the patient is informed whether he or she may be included, and the randomization procedure is performed. Following this, the remaining baseline measures are acquired (see Table 1). Those with scores below the BSSI threshold are excluded from the trial but will receive usual care within the clinic.

**Table 1 Tab1:** Measurements at follow-up

Measures	T1 baseline	T2: 3 weeks	T3: 6 months	T4: 12 months	Outcome (1–10 years)
Primary outcome measure					
Beck Scale for Suicide Ideation - Current (BSSI-C)	x		x	x	
Secondary outcome measures					
Suicide Attempt Self-Injury Count (SASIC)	x		x	x	
Outcome Questionnaire-45 (OQ-45)	x		x	x	
Norwegian Patient Registry data (specified below)					x
Potential moderators and descriptive measures					
MINI		x			
Structured Clinical Interview for ICD-10		x			
Treatment history interview - short form	x		x	x	
Generalized Self-Efficacy Scale (GSE)	x		x	x	
Working Alliance Inventory - Short Revised (WAI-SR Client)		x			
Alcohol/Drug Use Disorders Identification Tests (AUDIT and DUDIT)	x				

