#### Assessments and measurements

The test battery will be administered by four research assistants. Completion of the baseline and the first follow-up interview (T1, T2) will take approximately 50–70 minutes each. Follow-up screenings after 6 and 12 months each will take approximately 25–45 minutes. We will perform a screener crossover at T3 and T4 so that the research assistant who screens for follow-up is blinded for treatment condition. Treatment condition is not concealed or blinded for the patient or the clinician treating the patient.

The research assistants consist of experienced psychiatric research nurses and psychiatric research health workers and the first author (WR). All have been formally trained for conducting the diagnostic interviews, and one research nurse has previous experience with attending and screening in another research project. The diagnostic interview is conducted in the follow-up interview at T2, after inclusion. After conducting the clinical diagnostic interview, the research assistant discusses and clinically validates the diagnostic conclusion with the first author or with the experienced research nurse. Beyond this, a more formal reliability check on diagnosis will not be carried out. Data will be stored in paper form until all follow-up interviews are completed and then entered into digital form for statistical analysis.

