#### Potential moderators and descriptive measures

The *Mini International Neuropsychiatric Interview (MINI)* will be used at baseline to identify DSM-VI and ICD-10 disorders associated with mood and psychosis along with other disorders. Studies have shown a good reliability and validity compared with the CIDI and the SCID-I interview [30]. In addition, the Structured Clinical Interview for DSM-IV Axis II Borderline Personality Disorder (SCID-II) will be administered to identify patients with borderline personality disorder given the importance of this group in the suicidality literature [31].

The *Generalized Self-Efficacy Scale (GSE)* is a reliable and valid measure comprising 10 items assessing the strength of an individual’s belief in the ability to respond to novel or difficult situations and to deal with a large variety of stressors [32, 33]. The GSE will be administered at baseline and after 6 and 12 months.

The *Working Alliance Inventory - ShortRevised (WAI-SR)* is a 12-item measure that will be used to assess the patient’s and therapist’s alliance after their third session together [34]. We will use the patient version of the instrument, which has high internal consistency and correlates well with other alliance measures.

Substance abuse is assessed with the *Alcohol Use Disorders Identification Test (AUDIT)* [35] and the *Drug Use Disorders Identification Test (DUDIT)* [36]. The AUDIT includes 10 questions about patterns of alcohol use and dependence. The DUDIT includes 11 questions about use or abuse of a list of drugs. Both instruments have satisfactory psychometric properties in clinical and non-clinical samples, with overall reliability above .80 and convergent validity, sensitivity, and specificity above 85 % [37, 38]. AUDIT and DUDIT will be scored at baseline.

The *Suicide Status Forms (SSFs)* are administered (initial, tracking, and outcome versions) as part of the course of care in CAMS (used for CAMS condition only). The SSF has six core rating assessments derived from theoretical approaches of Shneidman, Beck, and Baumeister and has well-established reliability and validity [39, 40].

As two of the measures (SSI-C and SASIC) did not have a Norwegian version, they were translated according to conventional procedures.

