### Statistical analysis

We will use generalized linear regression to examine the effects of treatment condition (CAMS versus TAU) upon suicidal thoughts (SSI-C scores) and mental health functioning (OQ-45 scores). Possible moderator effects will be estimated by using an array of covariates, including baseline measures (age, gender, ethnicity, diagnoses, and psychological measures), working alliance, medication during the treatment period, varying treatment length, new treatments delivered during follow-up, and an eventual leakage of CAMS elements into TAU.

Statistical analysis will be by intention to treat. To manage and replace missing data, we will create several sets of plausible imputed data, based on the Bayesian approach, by using multiple imputation procedures for the variables of interest, following the guidelines of Sterne and colleagues [43]. In a further sensitivity analysis we will perform the analysis using the per protocol method, excluding patients who did not complete treatment or missed measurements.

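### Two exclusion rules can act after randomisation, and the plan does not say that the affected patients stay in follow-up or in the intention-to-treat set

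*Protocol article*

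**What the plan says.** The Exclusion criteria section of the protocol article contains two separate rules.

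- **Developmental or intellectual disorder.** Suspected cases are not recruited. For those found later: "If such information or diagnosis is made post hoc after inclusion, the participant will be excluded from further participation".
- **Psychosis.** Patients with active symptoms are not invited. Beyond that: "If such functioning is identified during the screening process (e.g., by MINI), the patient will be excluded from the trial".

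The order of events is given elsewhere.

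- Recruitment: after consent and a qualifying BSSI-C score, "At this point the patient is informed whether he or she may be included, and the randomization procedure is performed". Then: "Following this, the remaining baseline measures are acquired".
- Assessments and measurements: "The diagnostic interview is conducted in the follow-up interview at T2, after inclusion". Table 1 also places the MINI at T2, which is 3 weeks in that table and 2 weeks in the Abstract.
- Potential moderators and descriptive measures: the MINI "will be used at baseline to identify DSM-VI and ICD-10 disorders".

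On the analysis set, the Statistical analysis section states: "Statistical analysis will be by intention to treat". It plans multiple imputation for missing data and mentions exclusions only for a per-protocol sensitivity analysis.

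**The concern.** An exclusion decided after allocation is harmless to the comparison only if it cannot depend on the arm, or if the patient is still followed and analysed. The plan secures neither.

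Knowledge of the arm is available when these decisions are made. Treatment is not blinded for patients or treating clinicians, and the crossover of assessors that provides blinding is described for T3 and T4 only. Treatment is probably under way by T2, because Table 1 schedules there an alliance scale that is completed after the third session. The arms also differ in who treats: 8 of 9 CAMS therapists are psychologists, against 6 of 21 in TAU. The chance that a developmental or intellectual disorder is noticed during treatment may therefore not be the same in both arms.

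At stake are the comparability of the arms and the 6- and 12-month outcomes of patients already randomised, in a trial of 100.

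**Working it through.** **Step 1: does each rule act after randomisation?**

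| Rule | Trigger | Position relative to randomisation |
|---|---|---|
| Developmental or intellectual disorder | Diagnosis made after inclusion | After, by its own wording; MINI timing is irrelevant |
| Psychosis | MINI finding | After, if the MINI is at T2; also after, if it is at baseline, since all baseline measures other than the BSSI-C follow randomisation |

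The psychosis rule is worded as a screening rule, but as scheduled no MINI exists before allocation. The word screening does not settle the matter: the Assessments and measurements section also uses it for the 6- and 12-month interviews.

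**Step 2: what happens to the data?** No section says that excluded patients are interviewed at T3 and T4 or counted in the intention-to-treat set. If they are removed, the set is not all randomised patients. If they are kept with imputed outcomes, their later outcomes are still not collected. The imputation model would then see few or no observed outcomes among patients with the triggering diagnosis, so it would largely treat them like the others.

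**Step 3: the plan's own power figure.** Inputs from Power calculation: SD 7, difference 4, one-sided alpha 0.05, 80 analysed (40 per arm), 20% drop-out.

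- Standard error = 7 × √(2/40) = 1.565.
- Power = Φ(4/1.565 − 1.645) = Φ(0.911) = 81.9%, against 82% stated.
- 80/(1 − 0.20) = 100, as stated.

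The figures reproduce, and this point disputes none of them.

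**Step 4: possible bias (assumed inputs).** If a share p of an arm is removed and these patients average d points worse than those who stay, the arm mean falls by p × d. The treatment difference shifts by (p₁ − p₂) × d. The documents give neither p nor d, so both are assumptions.

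| p₁ | p₂ | Difference | d = 5 | d = 8 |
|---|---|---|---|---|
| equal | equal | 0 | 0 | 0 |
| 10% | 5% | 5 points | 0.25 | 0.40 |
| 10% | 2% | 8 points | 0.40 | 0.64 |

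The largest value, 0.64, is 0.64/4 = 16% of the target difference and 0.64/1.565 = 0.41 standard errors. The shift favours whichever arm loses more patients.

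**Step 5: equal exclusion (assumed numbers).** If exclusions come on top of 20 drop-outs and are equal across arms, power with n per arm = (80 − excluded)/2 is:

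| Excluded of 100 | n per arm | Power |
|---|---|---|
| 0 | 40 | 81.9% |
| 2 | 39 | 81.0% |
| 5 | 37.5 | 79.7% |
| 10 | 35 | 77.2% |

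If exclusions fall within the 20% allowance, they use it up instead.

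**The case against.** The strongest reply has four parts.

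- **The text may not remove anyone from the analysis.** Ending participation is not the same as leaving the analysis set, and intention to treat with imputation could cover these patients. This stands in part. A reader might infer that the plan breaks its intention-to-treat commitment, but the documents show an ambiguity, not a direct contradiction. The loss of T3 and T4 outcomes remains on either reading.
- **The psychosis rule may be a wording slip.** It is tied to screening and may never have been meant for T2. That is possible, but the published schedule leaves it nowhere else to act, so the sections need reconciling. It is right, however, that MINI timing bears on psychosis only. The article does not say that the MINI detects developmental or intellectual disorders.
- **Detection may be even across arms.** All patients get the same research battery from the same assistants. A reader might infer that exclusion will depend on the arm; nothing in the documents shows that it will. That T2 assessors are unblinded is also an inference from blinding being described only for T3 and T4.
- **Numbers should be small.** Patient records are checked beforehand, suspected cases are not recruited, and a clinician assesses each patient before invitation. This stands and limits the size of the problem.

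Consent is a further limit. The psychosis criterion is linked to the ability to consent, so continued interviews cannot be required unconditionally.

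**Conclusion.** The point holds as a defect in how post-randomisation exclusions are fixed. One rule explicitly acts after inclusion. The other does so because of where the MINI sits, whether at T2 or at baseline. Neither is tied to the stated intention-to-treat analysis, and outcomes of randomised patients would be lost.

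Arm-dependent exclusion is a risk only. Under the assumed differences of 0 to 8 percentage points, with excluded patients 5 to 8 points worse, bias runs from 0 to about 0.6 BSSI-C point. With equal exclusion the cost is mainly power, for example 81.9% to 77.2% for 10 exclusions on top of the planned drop-out. These sizes rest wholly on the assumptions, since the documents give no exclusion rate. The conclusion that the sections need reconciling does not depend on them.

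**What to change.** - State that every randomised patient stays in the primary intention-to-treat set, whatever diagnosis emerges later.
- State that such patients are interviewed at T3 and T4 where consent continues.
- Use later-found ineligibility only in a labelled sensitivity analysis, judged blind to arm and on information that existed before randomisation.
- Make Exclusion criteria, Table 1, Assessments and measurements, and Potential moderators and descriptive measures agree on when the MINI is done and whether it can decide eligibility.

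These changes concern data collection and the analysis set, not patients' care. The cost is some rewording, follow-up of a few patients who would otherwise be dropped, and a few ineligible patients in the primary set. Trial status reports that recruitment is still open, and 6- and 12-month outcomes that are not collected on time cannot be recovered, so the change is best made now.
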